#### Masking

Participants, therapists, and assessors involved in the study will be blinded to the treatment allocation. During the intervention, both active and sham tDCS conditions will have the electrodes applied in the same manner. However, in the sham condition, the stimulation will only be applied for the first 30 s to mimic the sensation of tDCS, after which no current will be delivered for the remaining session time.

The therapists administering the intervention will not have access to the allocation sequence and will perform the same proprioceptive exercises for all participants, regardless of the group. To prevent any bias, the individuals responsible for collecting and analyzing the data will also be blinded to group allocation.

#### Measures

##### Timed up and go test

The Timed Up and Go (TUG) test is widely used to assess functional mobility and consists of the time in seconds required to stand up from a standard chair, walk along a straight line for three meters, turn around, walk back to the chair, and sit down again. A longer time required to complete the task denotes poorer functional mobility. At the beginning of the test, the participant will be seated with the back against the backrest of the chair and must return to this same position at the end of the test. The test will begin with the command “Go”. The TUG test will be performed four times under the following conditions: in shoes with a cane; in shoes without a cane; barefoot with a cane; and barefoot without a cane. The participants will first be given a practice run to become familiar with the test. During the test, the G-sensor (BTS Bioengineering) will be used for the precise quantification of the time required to perform the task (30). We will analyze functional mobility throughout the variables such as: phase duration (s), acceleration, and velocity of the TUG, sit-to-stand, stand-to-sit, mid-turn, and end-turn.

##### Walk test

For the walk test, the participant will be instructed to walk along a straight line for seven meters. The test will be performed with an inertial sensor (G-Sensor®), which will collect spatiotemporal variables, general kinematic variables, symmetry index, propulsion index, and pelvic kinematics (31). Participants will perform the test three times and the mean of the trials will be used for statistical analysis.

##### G-Sensor

The G-Sensor® (BTS Bioengineering S.p.A. Italy) (32, 33) is a portable, wireless system of inertial sensors for human movement analysis. The device will be held in place by a specific strap, which will enable the participant complete freedom for walking, running, and jumping. The sensor sends all data to a computer via Bluetooth. At the end of each analysis, a detailed report is furnished on all variables recorded during the test. The sensors are controlled by a data recording unit (up to 16 elements) through ZigBee radio communication. Each sensor measures 62 × 36 × 16 mm, weighs 60 g, and is composed of a three-axis accelerometer (maximum scale: ±6 g), three-axis gyroscope (complete scale: ±300°/s) and three-axis magnetometer (complete scale: ±6 Gauss). The device is calibrated with the acceleration of gravity immediately after its fabrication. In the present study, the device will be used during the execution of the TUG test and Walk Test to obtain precise data on spatiotemporal variables and functional mobility. The data from the inertial sensor will be transmitted via Bluetooth to a computer and processed using the appropriate software (BTS G-STUDIO, version 2.6.12.0), which automatically furnishes the variables (32, 33).

The following information will be collected: stride length (m); gait speed: mean instantaneous velocity within the gait cycle (m s^−1^); cadence (number of steps per minute [steps min^−1^]; position and duration of the swing phase [expressed as the percentage of the gait cycle—the proportion of a gait cycle that involves the stance and swing phases (from toe off to heel contact of the same foot)]; duration of double support (duration of stance phase with both feet, expressed a percentage of the gait cycle); pelvic angulation (tile, obliquity and rotation) of stride (distance between two consecutive heel contacts).

##### Pediatric evaluation of disability inventory (PEDI)

The functional performance will be evaluated quantitatively using the Pediatric Evaluation of Disability Inventory (PEDI), which is a questionnaire administered in interview form to a caregiver with information on the child's performance regarding routine activities and tasks. The test is composed of three parts: the first part addresses skills in the child's repertoire grouped into three functional domains: self-care (73 items), mobility (59 items), and social function (65 items). Each item is scored either 0 (the child is unable to perform the activity) or 1 (the activity is part of the child's repertoire of skills). The scores are totaled per domain (34).

##### Pediatric balance scale (PBS)

The Pediatric Balance Scale (PBS) is a modified version of the Berg Balance Scale, specifically designed to assess balance in school-aged children with mild to moderate motor impairments (35). In this protocol study, we employed the Brazilian version of the PBS, which has been translated and culturally adapted for Brazilian populations (35). The PBS consists of 14 tasks that simulate daily living activities, each scored on a 5-point ordinal scale from 0 to 4, where: 0 = unable to perform the task independently; 1 = requires maximal assistance; 2 = requires moderate assistance or close supervision; 3 = minimal assistance or supervision; 4 = able to complete the task independently. The total score ranges up to 56 points, with higher scores reflecting better balance performance.

Below is a detailed description of the 14 tasks: Sitting to Standing; Standing to Sitting; Transfers (from sitting to lying); Standing Unsupported (up to 2 min); Standing with Eyes Closed (up to 10 s); Standing with Feet Together (up to 10 s); Standing with One Foot in Front (Tandem Stance); Standing on One Leg (up to 10 s); Turning 360 Degrees; Turning to Look Behind; Picking Up Object from Floor; Placing Alternate Foot on Step (Step-ups); Reaching Forward with Outstretched Arm While Standing; and Standing Unsupported, One Foot in Front on a Line (heel-to-toe stance) (36, 37). For this measure, all subjects will perform the PBS in barefoot conditions.

##### Assessment of balance with proprioceptive disturbance

The assessment of static balance with proprioceptive disturbance will be performed using the SMART-D 140® system (BTS Engineering) with two Kistler force plates (model: 9286BA). The acquisition frequency will be 100 Hz and the force will be captured by four piezoelectric sensors measuring 400/600 mm positioned at the extremities of the force plate. The data will be recorded and interpreted by a software program (SWAY; BTS 161 Engineering) integrated and synchronized with the SMART-D 140® system. The participants will be instructed to remain in a static standing position with arms alongside the body and head in the vertical position. Three measurements (45 s each) will be performed to collect postural balance of COP (95% confidence ellipse area; velocity, and RMS in anteroposterior and mediolateral directions) under four different conditions: static balance with proprioceptive disturbance (soft surface) and eyes open; static balance with proprioceptive disturbance and eyes closed; static balance on a firm surface with eyes open; and static balance on a firm surface with eyes closed.

##### Three-dimensional gait analysis and electromyography

Gait will be analyzed along a track measuring 90 centimeters in width by five meters in length. Gait analysis will be performed with the aid of the SMART-D 140® system (BTS Engineering), consisting of eight cameras sensitive to the infrared spectrum synchronized with a video system and computer (SMART-D INTEGRATED WORKSTATION® with 32 analog channels). Two force plates (Kistler, model 9286BA) will be used for the collection of the kinematic gait data, recording displacements of the center of pressure and contact time between the foot and surface of the force plate (38, 39). Therefore, a protocol was implemented whereby bone landmarks were located by manual palpitation by the principal investigator. Reflective markers were firmly attached to the skin with double-sided tape. During the analysis, the participants will be wearing bathing suits. Markers will be positioned according to the protocol described by Davis (39). A total of 22 spherical markers will be placed—three on the trunk, three on each thigh, three on each shin, and two on each foot.

Information will be collected on body mass, height, distance between anterior iliac crests posteriorly, leg length, knee diameter, and ankle diameter. After placing the markers, participants will be instructed to walk along the track with the two force plates positioned in the center. Upon stepping on the force plates, kinematic gait data will be collected and calculated by the video system (BTS, Milan, Italy) synchronized to the data collection system. The following indices will be analyzed based on the spatiotemporal variables (velocity, cadence, step length, stride length, stance phase, and swing phase) and joint angles at specific moments of gait (pelvis inclination, hip flexion-extension, knee flexion-extension, and ankle dorsiflexion-plantar flexion), as well as foot progression.

The electrical activity of the muscles will be collected simultaneously with the three-dimensional analysis of the gait by the electromyograph FREEEMG® (BTS Engineering) composed of eight amplifiers of bioelectric signals, bipolar electrodes with a total gain of 2,000x at a frequency of 20–450 Hz and data transmission wireless. The impedance and common mode rejection ratio of the equipment is >1,015 Ω//0.2 pF and 60/10 Hz 92 dB, respectively. The electrodes will be placed on the motor point of the muscles after cleaning the skin with 70% alcohol to reduce bioimpedance, following the guidelines of the Surface Electromyography for the Non-Invasive Assessment of Muscles (SENIAM) (40). All electromyographic data will be collected and digitized at 1,000 frames/second using the BTS MYOLAB® software program. The electromyographic data will be collected simultaneously with the kinematic readings and both sets of data will be managed by the BTS® system and Smart Capture® software. The electrodes will be attached to the rectus femoris, tibialis anterior, biceps femoris, and soleus muscles bilaterally. In total, a minimum of five walking attempts will be recorded. Of these five attempts, three readings will be considered three times so that the participant becomes familiar with the protocol. To ensure patient safety during the walk, a researcher will be responsible for directing patients through verbal stimuli.

To minimize potential bias, all standardized assessment protocols are designed to ensure accurate and reliable collection. In addition, several training sessions will be offered to assessors and therapists to ensure standardized treatment, assessment, and data analysis. The amount of training will depend on the raters' and therapists' familiarity with clinical scales and treatment techniques. Standard procedures should be followed during evaluation and treatment. There will be several meetings where the Principal Investigator will be briefed on current events and available for consultation with any questions or concerns. Although we attempted to blind patients, therapists, and raters, it is unlikely that patients and therapists would remain blinded during the course of this study due to the nature of the treatment applied. However, to ensure that the risk of bias remains low, patients will be registered in the database via a patient identification code so that raters are blinded during analysis. Only the principal investigator will be aware of the allocation.

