### Randomization and allocation to groups

Randomization will take place in blocks. Participants and investigators will be blind to the tDCS condition allocation. Individuals who meet the eligibility criteria will be randomly allocated to one of the four study groups using a digital randomization platform (http://www.randomization.com). An opaque and sealed envelopes will be used to conceal group information. After signing the informed consent, individuals will choose an envelope with the name of the group to which they will be assigned in phases 2 and 3. This step will be managed by a third person who is not part of the study. The groups will be divided according to the type of therapy: Group 1 (G1)—active tDCS combined with static proprioceptive exercises; Group 2 (G2)—sham tDCS combined with static proprioceptive exercises; Group 3 (G3)—active tDCS combined with dynamic proprioceptive exercises; Group 4 (G4)—sham tDCS combined with dynamic proprioceptive exercises.

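### The principal investigator is the one person who knows the allocation, yet also locates the landmarks for the 3D gait analysis, so data collection at the gait sessions after allocation is not blinded as claimed

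*Protocol article*

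**What the plan says.** Two sections of the protocol article promise wide blinding. Under Randomization and allocation to groups: "Participants and investigators will be blind to the tDCS condition allocation". Under Masking: "Participants, therapists, and assessors involved in the study will be blinded to the treatment allocation", and further, "the individuals responsible for collecting and analyzing the data will also be blinded to group allocation".

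The section Three-dimensional gait analysis and electromyography describes something else. For marker placement, "bone landmarks were located by manual palpitation by the principal investigator". The bias paragraph at the end of that section then states: "Only the principal investigator will be aware of the allocation". It also concedes, of families and treating staff, that "it is unlikely that patients and therapists would remain blinded during the course of this study". The protection it offers is that "patients will be registered in the database via a patient identification code so that raters are blinded during analysis".

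Three other statements bear on the point:
- Primary outcome measures lists three-dimensional gait analysis first, with gait speed, stride length, support phase and ground reaction force.
- Evaluation protocol repeats the assessments immediately after the intervention and 1 month later.
- Of the envelope step, Randomization and allocation to groups says: "This step will be managed by a third person who is not part of the study".

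**The concern.** Marker placement by palpation is a manual, operator-dependent step in an otherwise instrumented measurement. If the person doing it knows whether the child had active or sham stimulation, a difference between arms in marker-derived values could partly reflect how the markers were placed.

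This matters more here than in many trials. The article itself expects the blinding of patients and therapists to fail, so blinded outcome assessment is the main protection left. The plan gives the one declared unblinded role a hands-on task in collecting a primary outcome domain. Measurements taken this way cannot be repaired after the fact, and readers of the results would be told that data collection was blind.

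**Working it through.** No arithmetic applies, because the article gives no figure on this point. The check sets the statements side by side.

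1. **Who knows the allocation.** The bias paragraph names the principal investigator and excludes everyone else. Randomization and allocation to groups says that investigators are blind to the tDCS condition. The principal investigator is an investigator, so both statements cannot be true.

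2. **Who collects gait data.** The gait section gives landmark location to the principal investigator. Masking says that those who collect data are blind. Taken with step 1, this also fails.

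3. **When it happens.** Evaluation protocol sets three assessments: before the intervention, after it, and at 1 month. The last two certainly follow allocation. For the first, the article says that the envelope is chosen after consent but does not say whether the baseline assessment comes before or after that. The conflict is therefore established for two visits and open for the third.

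4. **Whether the stated safeguard covers it.** The identification code blinds raters during analysis. It does nothing at the measurement session, where the principal investigator is in contact with the child. No section withdraws the principal investigator from the sessions after allocation or delegates the landmark step.

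5. **Which outcomes the palpation route can reach.**

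| Measure | Source in the plan | Exposure to landmark placement |
|---|---|---|
| Joint angles | Markers; analysed, but not listed as primary | Main exposure |
| Stride length, other spatiotemporal values | Gait system; stride length and support phase primary | Lesser |
| Gait speed | Gait system; primary and one of two sizing outcomes | Little |
| Ground reaction force | Force plates; primary | None |
| Static centre-of-pressure displacement | Force plates, standing; primary | None; no landmark step described |
| Timed Up and Go time | Inertial sensor; primary | None |

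The exposure ratings are a judgement about measurement technique, not figures from the article.

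6. **Whether the principal investigator needs the allocation.** The article gives no reason. A person outside the study already manages the envelopes.

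**The case against.** Several objections have weight.

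- **The gait values come from an instrument.** The camera and force-plate system computes them, and the principal investigator is said to locate landmarks, not to score outcomes. This stands, and it limits the likely size of the bias. It does not make the blinding statements consistent.

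- **The outcomes that size the trial are largely out of reach.** A reader might infer that blinding fails for the outcomes on which Phase 3 is sized. The documents do not support that. Sample size and recruitment names gait speed and centre-of-pressure displacement. The first depends little on exact marker position, and the second is measured on force plates in static standing.

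- **Other routes are inference.** A reader might also suppose that the principal investigator chooses which walking attempts count, or guides staff differently by arm. The article does not say who selects attempts, and the person who directs the child verbally is an unnamed researcher. The principal investigator is only said to be briefed at meetings and available for questions. These are possibilities, not stated procedures.

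- **The likely unblinding is disclosed and may concern the exercises.** Exercise type cannot be hidden, and the article attributes the expected unblinding to the nature of the treatment without saying which component is meant. This is fair, but it makes the unqualified double-blind label in the Abstract and Study design harder to defend.

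- **The landmark sentence is in the past tense.** It still describes this study's own gait procedure, so the conflict remains.

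- **A fuller protocol might settle it.** The point is not an omission. The article makes statements that are incompatible with each other.

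**Conclusion.** The point holds as an internal contradiction with a practical consequence. As written, the claim that data collection is blinded is untrue for the three-dimensional gait sessions at the post-intervention and 1-month visits, because the one role said to know the allocation performs a manual step in them. Whether the baseline session is also affected cannot be told from the article.

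The size of any bias cannot be computed. Through palpation it would fall mainly on joint angles and to a lesser degree on stride length and other spatiotemporal values. Gait speed is little affected. Ground reaction force and static centre-of-pressure outcomes are not affected by this route. It would go too far to say that all primary gait outcomes, or both sizing outcomes, are compromised.

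This rests on two assumptions: that the principal investigator locates landmarks at every gait session, since no exception is stated, and that knowing the allocation means knowing active from sham stimulation, which the four group definitions imply.

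**What to change.** Reconcile Randomization and allocation to groups, Masking and the gait section so that nobody who knows the allocation takes part in measurement after allocation. Either arrangement would do:

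- **Blind the principal investigator.** The allocation is held only by the third person who already manages the envelopes and by whoever sets the stimulator to active or sham. The person setting the stimulator does no assessments. Naming that role matters, because the therapists are meant to stay blind and someone must set the device at each of the ten sessions.
- **Keep the principal investigator unblinded, but out of measurement.** Landmark location and the gait sessions go to one of the blinded assessors for whom training is already planned, the same one at all visits where possible.

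In either case, describe the trial as sham-controlled with blinded outcome assessment instead of using an unqualified double-blind label, since the article expects patient and therapist blinding to fail.

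The change should be made before Phase 2 enrols, because Phases 2 and 3 use the same methods. The cost is some rescheduling of roles, training of the chosen assessor in marker placement (the article mentions assessor training only in general terms), and routing of unblinding requests through the allocation holder. The active tDCS offered to sham participants at the end of the study would also have to be arranged through that holder.

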#### Outcome measures

##### Primary outcome measures

The primary outcomes focus on quantifying improvements in gait, balance, and functional mobility:

Instrumental Assessments:
1.Three-dimensional Gait Analysis:
○Gait speed (m/s)○Stride length (m)○Duration of the support phase (percentage of gait cycle)○Ground reaction force2.Balance (force platform):
○COP displacement along the *X* (anteroposterior) and *Y* (mediolateral) axes: Analyzed during static balance tasks performed with proprioceptive disturbance (soft and firm surfaces).
Clinical Assessments:
1.Timed Up and Go (TUG) Test:
○Time (seconds) to complete the TUG test under various conditions (with and without a guide stick, with and without shoes) to assess functional mobility.2.Electromyography (EMG):
○Muscle activity (µv)3.Pediatric Balance Scale (PBS):
○Assesses postural control with 14 tasks scored from 0 (unable to perform) to (independently performs). Maximum score: 56 points.

##### Secondary outcome measures

The secondary outcomes aim to provide additional insights into the overall impact of the intervention on daily function and postural control.

Instrumental Assessments:
1.G-sensor® Analysis:
○Assesses spatiotemporal gait parameters (e.g., cadence, step length, propulsion index) using a portable wireless G-sensor® device during walking tasks.Clinical Assessments:
1.Pediatric Evaluation of Disability Inventory (PEDI):
○Evaluates functional capabilities in three domains: self-care, mobility, and social function. Each item is scored from 0 (unable) to 1 (able).

#### Evaluation protocol

Evaluations will be performed in all phases of the study. Evaluations will be conducted before the intervention, immediately after the intervention, and 1 month after the end of the intervention.

#### Intervention protocol

The therapeutic intervention will consist of ten sessions of transcranial direct current stimulation, which will be applied using the Transcranial Stimulation device (Transcranial Technologies, USA) with two sponge (non-metallic) electrodes measuring 5 × 7 cm moistened with saline solution (41). Stimulation will be administered simultaneously during the protocols.

Each session will have a duration of 30 min, with the same session length for both active and sham stimulation protocols, ensuring a valid comparison. During the ten training sessions, tDCS will be administered with the anode positioned centrally over the cerebellum and the cathode positioned in the central supraorbital region. For sham stimulation, the electrodes will be positioned in the same way and the stimulator will be switched on for the first 30 s, giving the participant the initial sensation of stimulation, but no electrical current will be delivered for the remainder of the session. This is a valid control procedure for studies involving tDCS. In the active groups, a current of 1.5 mA will be administered for the stimulation of the cortices during the 20 intermediate minutes of each session. The stimulation device will automatically and gradually increase to 1.5 mA at the onset of treatment and gradually diminish in the final 10 s.

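### As written, sham current starts with the session and active current starts part-way through it, so the onset of sensation can differ by arm and could unmask people who know the schedule

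*Protocol article*

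**What the plan says.** The Intervention protocol section fixes the session length: "Each session will have a duration of 30 min, with the same session length for both active and sham stimulation protocols". For the sham groups it says that "the stimulator will be switched on for the first 30 s, giving the participant the initial sensation of stimulation". After that burst the text allows nothing further: "but no electrical current will be delivered for the remainder of the session". The Masking section repeats this: "in the sham condition, the stimulation will only be applied for the first 30 s to mimic the sensation of tDCS", with no current in the session time that remains.

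For the active groups the Intervention protocol section says that "a current of 1.5 mA will be administered for the stimulation of the cortices during the 20 intermediate minutes of each session". It then adds: "The stimulation device will automatically and gradually increase to 1.5 mA at the onset of treatment and gradually diminish in the final 10 s". It does not say whether onset and final refer to the session or to the 20-min window. The same section describes the sham procedure as a valid control for tDCS studies.

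On blinding, the Masking section states: "Participants, therapists, and assessors involved in the study will be blinded to the treatment allocation". The closing paragraph of the section on three-dimensional gait analysis and electromyography says instead that patients and therapists are unlikely to stay blinded, because of the nature of the treatment. It relies on coded records to keep raters blinded during analysis.

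**The concern.** A sham masks the arm only if it imitates what the active condition feels like and when. Here the sham burst is tied to the start of the session, while the active current is placed in the middle of it. Anyone who knows this and learns when a child felt tingling has a clue to the arm.

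The protocol gives that information a route to staff. Two physiotherapists accompany each child (Dynamic proprioceptive exercises; Adverse effects). Tingling and itching at the electrodes are listed as expected effects, and participants are told to report discomfort at once (Adverse effects). There are ten sessions per child, so the cue can recur.

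Active versus sham is the central comparison. Several primary outcomes depend on effort, among them TUG time, gait speed and the Pediatric Balance Scale. Coding the data for raters does not prevent differences in expectation or encouragement during training. The pilot uses the same methods as the main trial and supplies the data for its sample size, so any resulting bias could enter both the planned size and the final estimate.

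**Working it through.** No sample size or error rate is involved. The check is a timeline, with all inputs from the Intervention protocol section.

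**Inputs**
- Session length: 30 min, both arms.
- Active current: 20 min, described as intermediate; start minute not given. Call the lead-in L (min).
- Sham current: 30 s = 0.5 min, from minute 0 if counted against the session.

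**Formulae and results**
- Current-free time in an active session: 30 − 20 = 10 min.
- Active window: minute L to minute L + 20, leaving 10 − L min afterwards.
- For the window to be intermediate, both L and 10 − L must exceed 0, so 0 < L < 10.
- Difference in onset: L − 0 = L, so more than 0 and less than 10 min.
- Overlap of the sham burst with the active window: max(0, 0.5 − L). Any L of 0.5 min or more gives zero overlap.
- If the window is centred (assumption): L = 10 / 2 = 5. Active current runs from minute 5 to 25, sham from minute 0 to 0.5. Overlap is 0 and the onsets differ by 5 min.

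**Does the ramp sentence resolve it?**

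| Reading of the ramp sentence | Onsets across arms | Fit with the 20 intermediate minutes |
|---|---|---|
| Onset and final 10 s both refer to the session | Coincide | Conflict: current would span about 30 min, not 20 |
| Only onset refers to session start; 20 min of current | Coincide (L = 0) | Conflict: minutes 0 to 20 are not intermediate |
| Both refer to the 20-min window | Differ by L | Consistent |

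The only reading that fits the active-current sentence leaves the offset in place. A matched sham without conflict would require counting the sham 30 s from the start of the 20-min window. Neither section says that, and both describe what follows the 30 s as the rest of the session, which points to the session clock.

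**The case against.** The strongest reply is that this is loose drafting in a condensed article. Both sections say that the 30 s are meant to imitate the sensation of stimulation, so a matched onset was evidently the aim, and the device may in practice start at the same minute in both arms. That is plausible, and it is why the point concerns what the text prescribes rather than what will certainly happen. It does not remove the need to correct the text, because someone following it literally would deliver mismatched onsets.

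Other parts of the reply also stand:
- A reader might infer that a child can tell which arm they are in. The documents do not support this. The groups are parallel, each child feels one pattern during the trial, sham children receive active tDCS only at the end of the study, and nothing says families are told when to expect sensation.
- The therapist route is possible but not documented in full. The article does not say who operates the device, whether its running state can be seen, or whether therapists know the schedule.
- A reader might count the lack of a stated sham ramp as a defect. The ramp sentence names the device rather than an arm, and such settings are detail that an article may leave to the full protocol.
- The consequence for bias is not quantified. The primary outcomes also include COP displacement, ground reaction force and EMG, TUG time is recorded by a sensor, and assessors are stated to be blinded.

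The concession that blinding is unlikely to hold does not dispose of the point. It attributes the failure to the nature of the treatment, not to timing, and it conflicts with the Masking section.

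**Conclusion.** The point holds in limited form. On the literal wording of the Intervention protocol and Masking sections, the sham does not reproduce the active onset. The difference is more than 0 and less than 10 min; 5 min rests on the assumption that the 20 min are centred, and towards the lower end of the range the cue fades. Reading the ramp as beginning with the session removes the difference only by contradicting the statement that the 20 min are intermediate.

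This could unmask those who know the schedule, mainly therapists who see both arms and hear children's reports. It weakens the claim that the sham is a valid control. It would be too strong to say that timing reveals the arm: no start minute is given, and the route depends on reported sensations and knowledge of the schedule. The size of any bias cannot be derived from the documents. Separately, and without any assumption, the two statements on whether patients and therapists will be blinded contradict each other.

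**What to change.** Reconcile the Intervention protocol section, the Masking section and the blinding paragraph at the end of the gait analysis and electromyography section:

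- State the timing of current in both arms on one clock (session or stimulation period), with sham onset coinciding with active onset at whatever minute the sponsor sets, and say which clock the ramp sentence uses.
- Make the blinding claim consistent throughout, naming who is expected to remain blinded and who is not.

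Current, duration and ramp settings are for the sponsor to decide.

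The cost is a wording amendment and a check that the device's sham setting does what the text says. It needs no extra participants, visits or staff. The article does not describe the device's sham mode, so whether a setting must change is for the sponsor to establish. This is best done before Phase 2 data are used to size Phase 3. Aligning the onsets removes one avoidable cue; it does not by itself secure the blinding that the article elsewhere doubts.
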